## Results

Patient enrollment took place from September 2020 to April 2021, with a total of 139 patients enrolled, including 45 and 94 patients treated with 1.1 and 3.7 GBq ^131^I, respectively.

Characteristics of the study participants are displayed in Table 2. The START sample is composed of a large majority of women, with an average age of 47 years (range 18.70-81.80 years). All patients underwent total thyroidectomy with a diagnosis of differentiated thyroid cancer confirmed by pathological examination; the highest proportion in the TNM classification was Tx-T2, followed by Nx-N0, N1, T3, and T4, including approximately 47% of patients with residual thyroid tissue. The ^131^I-therapy was performed an average 4.11 (SD 3.91) months after the surgery (range 1-35 months). The majority of the included patients were treated for a papillary thyroid cancer.

Concerning the saliva samples, the mean pH was 7.34 (SD 0.48; range 6.00-8.50), with flow rates of 0.76 (SD 0.46; range 0.04-3.00) mL/min and 2.13 (SD 0.88; range 0.40-4.82) mL/min for unstimulated and stimulated saliva, respectively.

Statistically significant differences between the 1.1 and 3.7 GBq treated groups were found in saliva pH and nonstimulated saliva volume.

At the enrollment visit, among all 139 patients, 19 (13.6%) patients had suspicious or obvious symptoms of depression, whereas 67 (48.2%) patients had suspicious or obvious symptoms of anxiety according to the Hospital Anxiety Depression scale (see Table S1 in Multimedia Appendix 3).

When asked if patients experienced changes after thyroid removal surgery, 25 (18.0%) had the sensation of a dry mouth, 48 (34.5%) said they drink more often, and 27 (19.4%) were eating less salty foods.

Regarding lifestyle habits, among the 139 patients, 95 (68.3%) had never smoked, compared to 28 (20.1%) exsmokers and 16 (11.5%) current smokers; 87 (62.6%) never drink alcohol, compared to 45 (32.4%) being occasional drinkers (1-7 drinks/week) and 7 (5.0%) being regular drinkers (7-14 drinks/week) (see Table S1 in Multimedia Appendix 3).

Regarding radioiodine activity, the average doses recorded by the thermoluminescent dosimeters are presented in Table 3. Preliminary results based on the numerical calibration of the dosimeters in terms of cumulated activity provide absorbed doses to the salivary glands after application of the S-factor (self-dose) for salivary glands. There were 43 and 127 patients for which dosimeters were readable in the 1.1 GBq group and 3.7 GBq group, respectively. The doses to the salivary glands were approximately 3-times higher in the 3.7 GBq group than in the 1.1 GBq group (Table 3). For the whole group, the dose to the salivary glands per unit administered activity was 0.63 (SD 0.24) Gy/MBq. The ratio of left/right salivary glands cumulated activity was 0.97 (SD 0.15).

**Table 2 table2:** Characteristics of the study population.

Characteristics			1.1 GBq group (n=45)		3.7 GBq group (n=94)		Total (N=139)		*P* value^a^
**Gender, n (%)**									.24
	Women	35 (78)		64 (68)		99 (71.2)			
	Men	10 (22)		30 (32)		40 (28.8)			
Age (years), mean (SD)			47.16 (13.86)		47.02 (14.36)		47.07 (14.15)		.96
BMI, mean (SD)			26.88 (5.93)		27.14 (6.12)		27.06 (6.04)		.82
**Histology, n (%)**									.02
	Follicular	2 (4)		18 (19)		20 (14.4)			
	Papillary	43 (96)		76 (81)		119 (85.6)			
**pTNM^b^ staging, n (%)**									<.001
	Tx-T2	44 (100)		59 (63)		103 (74.6)			
	T3	0 (0)		33 (35)		33 (23.9)			
	T4	0 (0)		2 (2)		2 (1.5)			
	Nx-N0	38 (84)		40 (43)		78 (56.1)			
	N1	7 (16)		54 (57)		61 (43.9)			
**TSH^c^ elevation protocol, n (%)**									<.001
	L-thyroxin replacement stop	0 (0)		49 (52)		49 (35.2)			
	rTSH^d^	45 (100)		45 (48)		90 (64.8)			
**Thyroid remnant tissue, n (%)**									.07
	No	29 (64)		45 (48)		74 (53.2)			
	Yes	16 (36)		49 (52)		65 (46.8)			
**Family history of thyroid cancer, n (%)**									.66
	No	37 (82)		80 (85)		117 (84.2)			
	Yes	8 (18)		14 (15)		22 (15.8)			
**History of systemic disease, n (%)**									.19
	No	31 (69)		66 (70)		97 (69.8)			
	Type 2 diabetes	3 (7)		2 (2)		5 (3.6)			
	Dyslipidemia	3 (7)		3 (3)		6 (4.3)			
	Diagnosed hypertension	6 (13)		22 (23)		28 (20.1)			
	Sjögren syndrome	0 (0)		1 (1)		1 (0.7)			
	Brain tumors	1 (2)		0 (0)		1 (0.7)			
	Other	1 (2)		0 (0)		1 (0.7)			
**History of salivary dysfunctions, n (%)**									.15
	No	41 (91)		91 (97)		132 (95.0)			
	Yes	4 (9)		3 (3)		7 (5.0)			
Delay between surgery and RAI^e^ therapy (months), mean (SD)			4.98 (5.15)		3.69 (3.09)		4.11 (3.91)		.07
Unstimulated saliva flow (mL/min), mean (SD)			3.13 (1.82)		4.12 (2.47)		3.8 (2.32)		.02
Stimulated saliva flow (mL/min), mean (SD)			9.65 (3.18)		11.12 (4.83)		10.65 (4.41)		.07
**Dry mouth sensation after treatment, n (%)**									.67
	Yes	9 (20)		16 (17)		25 (18.0)			
	No	36 (80)		78 (83)		114 (82.0)			
**Saliva pH, mean (SD)**			7.2 (0.42)		7.41 (0.50)		7.34 (0.48)		.02
**Dry eye (OSDI^f^), n (%)**									.29
	Normal	34 (79)		78 (86)		112 (83.6)			
	Light	3 (7)		8 (9)		11 (8.2)			
	Mild	4 (9)		2 (2)		6 (4.5)			
	Severe	2 (5)		3 (3)		5 (3.7)			

^a^*P* values are based on the *t* test for continuous variables or the *χ*^2^ test for categorical variables.

^b^pTNM: pathological tumor-node-metastasis.

^c^TSH: thyroid-stimulating hormone.

^d^rTSH: recombinant thyroid-stimulating hormone.

^e^RAI: radioactive iodine.

^f^OSDI: Ocular Surface Disease Index.

**Table 3 table3:** Dosimetry description.

Variables	1.1 GBq group (n=45)	3.7 GBq group (n=94)
Recorded doses at the left earlobe [Hp(0.07), mSv], mean (SD)	30.07 (9.81)	104.38 (35.43)
Recorded doses at the right earlobe [Hp(0.07), mSv], mean (SD)	30.74 (8.88)	107.72 (42.66)
Recorded doses at the sternal fork [Hp(0.07), mSv], mean (SD)	49.88 (31.47)	173.33 (94.2)
Absorbed doses to the salivary glands (mGy), mean (SD)^a^	702.00 (310.00)	2316.00 (784.00)

^a^N=127.

Further results should be published in 2022. These will be based on comparisons of data from questionnaires and saliva samples between T0 and T6. Individual factors associated with salivary dysfunctions will be presented, as well as the dose-response relationship between absorbed doses to the salivary glands and salivary dysfunctions at T6 and T18.

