#### Descriptive Analyses

The description of the population (means, SDs, and percentages) at baseline (before ^131^I-therapy) is presented in this paper. Comparison tests have been performed (*t* test and *χ*^2^ tests) between the two groups of patients (1.1 GBq and 3.7 GBq groups) at T0. This is based on medical and individual data collected in the questionnaire, the ^131^I dose received precisely at the salivary glands in comparison with the delivered activity, saliva flow descriptions, and responses to the questionnaires.

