**Adjustment factors to be tested**
Gender, self-rated menopausal status, age, BMI, histology, thyroid remnant tissue, pathological tumor-node-metastasis staging, thyroglobulin stimulation protocol, salivary comorbidities, medication intake, tobacco and alcohol consumption, surgery to therapy duration (months), family history of thyroid cancer

All statistical analyses will be performed using SAS statistical software for Windows (SAS Institute, Cary, NC). An α level of .05 will be accepted as significant.

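### Table 2's P values come from pooled-variance t tests; for stimulated saliva flow the spreads differ, and the Welch test gives P=.03 where .07 is printed

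*Protocol article*

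**What the plan says.** Under Descriptive Analyses, the article reports t tests and chi-square tests "between the two groups of patients (1.1 GBq and 3.7 GBq groups) at T0". The Table 2 footnote says that P "values are based on the *t* test for continuous variables". Neither place says whether equal variances were assumed. The significance level is given at the end of the planned analyses: "An α level of .05 will be accepted as significant".

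Table 2 prints P=.02 for unstimulated flow, P=.07 for stimulated flow (in the row "Stimulated saliva flow (mL/min), mean (SD")), P=.02 for saliva pH and P=.07 for the delay from surgery to radioiodine. After the paragraph on saliva samples, the Results text concludes: "Statistically significant differences between the 1.1 and 3.7 GBq treated groups were found in saliva pH and nonstimulated saliva volume". Stimulated flow is not named.

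The Textbox lists the t test again among the methods for continuous outcomes, without a variant. Its adjustment factors to be tested do not include baseline salivary flow.

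**The concern.** The pooled t test relies on equal variances, and with group sizes of about 1:2 it tolerates departures poorly. If the larger group has the larger variance, the pooled standard error is too large and P is too high. The SDs printed for stimulated flow, 3.18 and 4.83, show that pattern.

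Stimulated flow is one of the measurements behind the primary endpoint, through its cut-off of 0.7 mL/min at T6. The activity groups are not randomised, and administered activity is a factor of interest. If the 3.7 GBq group starts with higher flow on both measures, it has further to fall before crossing a fixed cut-off, which could hide part of an activity effect at T6. A reader who sees only one flow measure flagged at T0 has less reason to adjust for both.

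**Working it through.** **Inputs.** Group sizes are from the Results ("including 45 and 94 patients treated with 1.1 and 3.7 GBq" of iodine-131). Means, SDs and printed P values are from Table 2. Tests are taken as two-sided, which the article does not state.

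**1. Reproduce the printed P for stimulated flow (pooled).**
- Pooled variance = (44 × 3.18² + 93 × 4.83²) / 137 = 19.08.
- SE = √[19.08 × (1/45 + 1/94)] = 0.792.
- t = (11.12 − 9.65) / 0.792 = 1.47 / 0.792 = 1.86 on 137 df, P = .066. This rounds to the printed .07.

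**2. Check that the other rows were pooled too.**

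| Row | Printed | Pooled | Welch |
|---|---|---|---|
| Stimulated flow | .07 | .066 | .035 |
| Unstimulated flow | .02 | .018 | .009 |
| Saliva pH | .02 | .016 | .011 |
| Delay, surgery to therapy | .07 | .068 | .126 |

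All four match the pooled column only. Age (.957 and .956) and BMI (.813 and .811) do not separate the two tests.

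**3. Compare the spreads for stimulated flow.** Variance ratio = (4.83 / 3.18)² = 2.31; the F test on 93 and 44 df gives P = .003. That test is sensitive to skewness, so the ratio itself is the main evidence.

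**4. Welch test for stimulated flow.**
- SE = √(3.18²/45 + 4.83²/94) = √(0.2247 + 0.2482) = 0.688.
- Pooled SE / Welch SE = 0.792 / 0.688 = 1.15, so the pooled SE is about 15% too large.
- t = 1.47 / 0.688 = 2.14 on 123.6 df, P = .0345.
- 95% CI for the difference: 0.11 to 2.83.

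**5. How far off the pooled test is.** In simulated normal data with no true difference, these SDs and these group sizes, the nominal 5% pooled test rejects about 2.4% of the time and Welch about 4.9%.

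**6. Sensitivity.**
- Rounding of the printed means and SDs moves the Welch P only between .033 and .036.
- If some saliva samples were missing: n=43 and 91 gives pooled .072, Welch .038; n=40 and 85 gives .082 and .045; n=38 and 80 gives .091 and .052. The last two would print as .08 and .09, not .07.
- Table 2's total flows (3.8 and 10.65) are five times the rates in the text (0.76 and 2.13 mL/min). A constant factor leaves every P unchanged. If the factor of 5 applies throughout, the difference is 1.47 / 5 = 0.29 mL/min.

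**7. The delay row.** The Results give a range of 1 to 35 months.
- A 35-month value in the 3.7 GBq group would contribute (35 − 3.69)² × 94/93 = 991 to a sum of squares that totals only 93 × 3.09² = 888. That is impossible, so the value is in the 1.1 GBq group.
- There it contributes (35 − 4.98)² × 45/44 = 922 of 44 × 5.15² = 1,167. Without it the SD falls from 5.15 to √[(1,167 − 922)/43] = 2.4, below the other group's 3.09.

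The variance ratio of 2.8 in that row, (5.15/3.09)², therefore rests on one patient.

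**The case against.** The strongest reply is that nothing is miscalculated: a t test was announced and .07 is a correct Student t test. That is so. The fault lies in the choice of variant given the table's own SDs.

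Second, the means, SDs and P are all printed, so nothing is concealed. A reader might infer that the article declares stimulated flow not to differ; it does not say so. It says that differences "were found in saliva pH and nonstimulated saliva volume", and that sentence is not a full list of T0 differences, since histology, staging and the TSH protocol also have P values below .05 and are not in it. As a statement on the saliva measures, however, it is incomplete once the right test is used.

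Third, several wider consequences are tempting but unsupported:
- *The primary result is affected.* The T0 tests are descriptive, and the primary endpoint is categorical and uses flow only through cut-offs at T6. Mean stimulated flow at T0, 2.13 mL/min, is about three times the 0.7 cut-off.
- *The T0 to T6 comparisons inherit the fault.* They are planned as paired tests, which make no assumption of equal variances between groups. Only an unpaired t test between activity groups could inherit it.
- *The delay would fail a 10% screen.* That threshold applies to univariate regressions on outcomes, not to Table 2, and delay is already a listed adjustment factor.
- *The delay row is a second clean example of unequal variances.* It depends on one extreme value, and neither t test summarises it well.

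Fourth, the number of saliva samples analysed is not stated, and the eye-dryness counts in Table 2 do fall short of 139 (43 and 91). Welch would exceed .05 at n=38 and 80, but the printed .07 does not fit losses that large.

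**Conclusion.** The point holds as a limited correction to a descriptive table. The printed P values fit only the pooled test. For stimulated flow that test overstates the standard error by about 15%, and the Welch result is P=.03 (difference 1.47 in the table's units, 95% CI 0.11 to 2.83), below the article's .05 level. Both flow measures are then higher at T0 in the 3.7 GBq group; unstimulated flow and pH stay significant.

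This rests on three assumptions: that the pooled variant was used (inferred from four of four informative rows), that saliva data are close to complete, and that tests are two-sided. The raw distributions are not shown. No primary result is wrong, and the size of the imbalance matters more than which side of .05 it falls on. The lasting consequence is that baseline flow is collected but is not among the listed adjustment factors.

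**What to change.** 1. Name the Welch t test for unpaired comparisons of continuous variables between the 1.1 and 3.7 GBq groups, in Table 2 and for any such t test under the Textbox.
2. Restate stimulated flow as P=.03, with the difference and its interval, and add it to the Results sentence on T0 saliva differences. Update the other Welch values (unstimulated flow .009, pH .01).
3. For the delay, report the median and range or a rank test, and do not rely on either t test.
4. Add baseline unstimulated and stimulated flow to the adjustment factors for the T6 flow and dysfunction models by administered activity or gland dose.

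The paired T0 to T6 tests need no change. The cost is close to nil: Welch is a routine alternative to the pooled test, the T0 flows are already collected, and the adjustment adds two covariates.

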## Discussion

Since many patients treated with ^131^I for thyroid cancer report salivary disorders, interfering with their quality of life, the START study was launched to detect and evaluate early and mid-term radiation-induced toxicity after ^131^I-therapy based on a prospective self-controlled study of patients with thyroid cancer. As an original multidisciplinary approach, the START study was designed to combine both objective and subjective parameters of quality of life with clinical and genetic information based on precise dosimetry, which better reflects the heterogeneity of the dose absorbed by the salivary glands. The use of several dosimeters makes it possible to discriminate the contribution coming from the thyroid remnants, after calibration under representative geometrical conditions. This approach further avoids having to perform several imaging examinations for the patients, and to integrate, de facto, the temporal variations of the activity in the salivary glands.

Moreover, this study will be the first to evaluate the genetic and epigenetic variants involved in salivary dysfunctions in patients treated with ^131^I, which may help to understand some of the biological mechanisms involved in radiation-induced sensitivity. These results should help to better estimate the individualized risk of long-term salivary dysfunctions after ^131^I-therapy, and thus allow the consideration of potential adverse effects in the choice of treatment.

As the study is still ongoing, this paper presents the protocol and objectives of the START study, as well as descriptive analyses of the included population and the doses recorded by the dosimeters. It is noteworthy that the sex ratio in the study reflects that of the population treated in nuclear medicine departments, which allows for an accurate estimation of the incidence of salivary disorders [22]. Regarding dosimetry, it can be observed that the recorded doses are highly correlated to the administered activities, with a strong earlobes left/right symmetry.

The START study is carried out in collaboration with the Pitié-Salpêtrière Hospital Group, which is the largest European center for the treatment of thyroid cancer, with 10 to 12 patients per week treated with ^131^I-therapy in the nuclear medicine department. The main limitation of this study is the potentially small number of patients presenting posttherapy salivary dysfunctions. However, the number of subjects to be included was calculated on the basis of 80% statistical power with a first-order risk of 5% and percentages of salivary dysfunctions estimated from the literature [4,20,21]. Nevertheless, salivary complications following ^131^I-therapy have been poorly studied, and the incidence rate is not very well estimated.

This study will help to deepen knowledge on the risks of salivary dysfunctions after ^131^I-therapy, as well as provide a better understanding of involved genetic factors. The findings will help target patients at risk of developing salivary dysfunctions and possibly adapt the treatment, thus improving the quality of life and nutritional status of patients with thyroid cancer.

## Appendix

Multimedia Appendix 1 Questionnaires.

Multimedia Appendix 2 Saliva sampling.

Multimedia Appendix 3 Table S1.

## Abbreviations

^131^I: radioiodine
START: Salivary dysfuncTions After Radioiodine Treatment
T0: baseline enrollment
T6: 6-month follow-up
T18: 18-month follow-up
TNM: tumor-node-metastasis staging
